#### **14.7 The level of statistical significance**

The type I error rate for interim analysis will be set to 0.001 in accordance with the Haybittle-Peto stopping boundary. For final analysis, the type I error rate will be set at 0.05. Confidence intervals will be reported at a 95% confidence level.

#### **14.8 Criteria for the termination of the trial**

Interim analysis of the primary outcome and the important secondary outcome of death before hospital discharge will be performed on half of the planned sample (126) by a DSMB. The Haybittle-Peto boundary will be used as a stopping rule. Therefore, the DSMB may recommend terminating the study early for large and statistically significant differences ( $p < 0.001$ ) between groups in the primary outcome or in the important secondary outcome of death before hospital discharge; or for unanticipated concerns regarding the safety of enrolled infants.

#### **14.9 Procedure for accounting for missing, unused and spurious data**

All data will be checked for missing values and followed-up to obtain data where possible. Missing data will be summarized by variable and by treatment group.

Missing values will be checked for processes possibly affecting missing data i.e. non-MCAR (Missing Completely at Random) processes correlated with outcomes. The method for handling missing data will then be specified accordingly in the Statistical Analysis Plan (SAP) before the database is locked.

Spurious or anomalous data will also be queried and corrected if found to be incorrect. No data will be excluded as outliers. However, statistical methods (rank-based methods) may be used to describe the data if outliers exist and adversely affect statistical analysis.

In compliance with the ethical conduct of RCTs, no data collected will be unused: all data will be described.

#### **14.10 Procedure for reporting any deviation(s) from the original statistical plan**

Any deviation(s) from the original Statistical Analysis Plan should be described and justified in the final report.

### **15 DIRECT ACCESS TO SOURCE DATA/DOCUMENTS**

Direct access will be granted to authorised representatives from the sponsor, host institution and the regulatory authorities to permit trial-related monitoring, audits and inspections.

### **16 DATA HANDLING AND RECORD KEEPING**

A data capture system is going to be used for this study. A case report form (CRF) is designed to record the data required by the protocol and collected by the investigator in the patient's clinical source

documents. Source documents for this study will include hospital records and procedure reports and data collection forms.

Data will be coded. It will be stored in a locked filing cabinet then uploaded onto a password-protected computer in a locked office.

#### **16.1 Data collection, source documents and case report forms (CRF)**

Source documents for this study will include hospital records and procedure reports and data collection forms. These documents will be used to enter data on the CRFs.. Participants who are transferred to another hospital before discharge home may have the following data points outstanding at the time of their transfer:

- Death before hospital discharge
- Survival without BPD at hospital discharge
- Survival without CLD at hospital discharge
- Duration of hospitalisation
- Use of home oxygen therapy

The PI at the study site, or their delegate(s), will collect outstanding data in consultation with colleagues at the destination hospital and enter it in the participant's record at the study site. This data will be used to populate the CRF.

All data entered on CRFs must be entered legibly. If an error is made, the error will be crossed through with a single line in such a way that the original entry can still be read. The correct entry will then be clearly inserted, and the alterations will be initialled and dated by the investigator. Data reported on the CRF that are derived from source documents must be consistent with the source documents or the discrepancies must be explained.

All documents will be stored safely in confidential conditions. On all study-specific documents other than the signed consent, the subject will be referred to by the study subject identification number/code.

#### **16.2 Data reporting**

Data are collected via paper CRF initially and then transferred to a computer to be stored in a secure database. Subjects will be identified by a code in the database. The name and any other identifying detail will not be included in any study data electronic file.

For data collected in the CRF, the sponsor is responsible for data processing including data validation and coding performed according to a specification manual that describes the checks to be carried out. As a result of data validation, data may require some changes. An electronic data clarification form is sent to the investigator who is required to respond to the query and make any necessary changes to the data.

When data validation is achieved, a blind review of the data is performed according to the sponsor standard operating procedure. When the database has been declared to be complete and accurate, it will be locked and made available for data analysis.

### **17 RETENTION OF ESSENTIAL DOCUMENTS**

Essential documents will be retained until at least 15 years after the publication of the clinical study report. These documents should be retained for a longer period however if required by the applicable regulatory requirements or by an agreement with the sponsor.

The investigator/institution should agree to retain the trial-related essential documents as required by the applicable regulatory requirements and until the sponsor informs the investigator/institution these documents are no longer necessary.

### **18 QUALITY CONTROL AND QUALITY ASSURANCE PROCEDURES**

This study will examine the off-label use of a licensed product. Curosurf is licensed for the treatment of infants born at 24 – 31 weeks gestation who are at risk of RDS; however, it is not licensed for oropharyngeal administration nor for infants born at < 24 weeks gestation that are offered intensive care who may be enrolled to this study. This study will thus be classed as a trial of an Investigational Medicinal Product (IMP) and will be subject to the relevant legislation and regulated by the competent authorities [e.g. Health Products Regulatory Authority (HPRA, <https://www.hpra.ie/>) in Ireland] in the

jurisdictions where the trial is performed. Standard procedures for reporting adverse event will be used in accordance with Good Clinical Practice (GCP) guidelines.

The investigator agrees, when signing the Study Protocol, to adhere to the instructions and procedures described in it and to the principles of GCP to which it conforms. The regulatory permission to perform the study will be obtained in accordance with applicable regulatory requirements. All ethical and regulatory approvals must be available before a patient is exposed to any study-related procedure, including screening tests to determine eligibility.

The investigator will allow the monitor to visit the site and facilities where the study will take place in order to ensure compliance with the protocol requirements and ICH GCP.

Training sessions may be organised for the investigators and/or instruction manuals may be given to the study team as required.

In addition, interim analysis of primary outcome and selected secondary outcome data will be performed on half the planned sample (126) by an external data safety monitoring board. They may recommend terminating the study early for large and statistically significant differences (e.g.  $P < 0.01$ ) between the groups in the primary outcome that demonstrate efficacy; or for unanticipated concerns for the safety of enrolled infants.

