### 14.2 Determination of sample size subjects

In randomised studies, the rate of mechanical ventilation in the days after birth among preterm infants treated with CPAP alone has varied from 46– 60%. (2, 11, 19-21) Minimally invasive surfactant techniques were shown to reduce the rate of mechanical ventilation to from 46% to 28% in a cohort of infants with a gestational age between 26 and 28 weeks. (21)

Sample size for this study was calculated in G\*power, using a two-sided, two-proportion Z test. To detect a difference in the rate of endotracheal intubation for respiratory failure of 18% between treatment arms (assuming a rate of 46% in the control group and 28% in the intervention arm) with 80% power and a 5% significance level, a sample size of 224 infants would be required. To compensate for a death rate of 10% (estimated from local data, The National Maternity Hospital, Neonatal Clinical Report for 2015) before the primary outcome can be determined (i.e. at 120 hours), we will need to recruit a total of **250** infants to this study.

The National Maternity Hospital is a stand-alone university maternity hospital with a tertiary NICU to which > 150 infants < 1500g are admitted annually. We have a track record of initiating, conducting, completing, presenting and publishing investigator-led randomised controlled trials, including trials that compared delivery room interventions, (12-14) trials that had respiratory failure in the NICU as the primary outcome (15) and trials that compared investigational medicinal products (16) in preterm infants. Though the enrolment rates to our studies amongst eligible infants are consistently excellent (> 80%), we believe it will be necessary to enrol infants at multiple sites in order to enrol our planned target sample of 250 infants in a timely fashion. We have a track record enlisting the help of collaborators

nationally(16)andinternationally(14, 17)to perform our studies. We believe that with their help, we can enrol these infants in 2–3 years.

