### 2.3 Statistical interim analyses and stopping guidance

Efficacy interim analysis of the primary outcome and the important secondary outcome of death before hospital discharge will be performed on half of the planned sample (126 subjects) by a DSMB. The Haybittle-Peto boundary will be used as a stopping rule. Therefore, the DSMB may recommend terminating the study early for large and statistically significant differences ( $p < 0.001$ ) between groups in the primary outcome or in the important secondary outcome of death before hospital discharge; or for unanticipated concerns regarding the safety of enrolled infants.

The type I error rate for interim analysis will be set to 0.001 in accordance with the Haybittle-Peto stopping boundary. For final analysis, the type I error rate will be set at 0.05. Confidence intervals will be reported at a 95% confidence level.

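### Protocol section 18 illustrates the interim efficacy threshold as P<0.01, against the Haybittle-Peto P<0.001 rule stated everywhere else for the same look

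*Combined protocol and SAP*

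**What the plan says.** Protocol 14.7 is prescriptive: "The type I error rate for interim analysis will be set to 0.001 in accordance with the Haybittle-Peto stopping boundary". Protocol 14.8 says the interim analysis "will be performed on half of the planned sample (126) by a DSMB" and makes Haybittle-Peto the stopping rule, at P<0.001, for the primary outcome and for death before hospital discharge. Protocol 11.4.1 and 13.5 give the same figure, as do SAP 2.3, 3.1, 5.2 and 5.2.1. The final test takes no deduction for the look; SAP 2.3 reads: "For final analysis, the type I error rate will be set at 0.05".

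Protocol section 18, on quality control and quality assurance, describes the same board and the same 126 infants. There the board may recommend early stopping for differences introduced with an e.g. and given as "P < 0.01$ ) between the groups in the primary outcome that demonstrate efficacy". It says that selected secondary outcome data will also be analysed, but does not name the outcome and attaches no threshold to it. Safety concerns are a separate ground, without a P value.

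This is operative version 2.1 text, not the document history. SAP section 6 reports consistency with the main features of the protocol's methods and does not mention the difference.

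**The concern.** An interim result with P between 0.001 and 0.01 is exactly the case that a stopping rule should settle in advance. Under protocol 14.8 it does not cross the boundary; under section 18 it matches the example of a result that may justify stopping for efficacy. Caregivers are not masked in this trial, which adds to the value of a single unambiguous rule.

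The two figures also differ in what they imply for the final test. Leaving the final level at 0.05 costs almost nothing after a look at 0.001, and somewhat more after a look at 0.01. What is at stake is mainly the decision to stop at half the sample, and to a smaller degree the overall false-positive rate.

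**Working it through.** **Inputs.** Test: "using a two-sided, two-proportion Z test" (protocol 14.2). Rates: "assuming a rate of 46% in the control group and 28% in the intervention arm" (14.2). Allocation 1:1 (11.3.6). Interim at 126 of 250, so the information fraction is 126/250 = 0.504. Two-sided critical values: 3.291 for 0.001, 2.576 for 0.01, 1.960 for 0.05.

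**1. The plan's own figure.** Protocol 14.2 states "with 80% power and a 5% significance level, a sample size of 224 infants would be required". With pooled variance and mean rate 0.37:

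n per arm = [1.960·√(2·0.37·0.63) + 0.8416·√(0.46·0.54 + 0.28·0.72)]² / 0.18² = 111.75, so 112 per arm and 224 in total.

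This agrees. 224/0.9 = 248.9, so 249 against the planned 250, which also agrees.

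**2. Overall type I error.** Under no effect, the interim and final statistics (Z1, Z2) are bivariate normal with correlation √0.504 = 0.710. With benefit taken as positive:

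overall error = 1 − P(−c_harm < Z1 < c_benefit and |Z2| < 1.960)

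| Interim rule | Overall two-sided error | Final level that would hold 5% |
|---|---|---|
| 0.001, both directions | 0.0502 | 0.0498 |
| 0.01 for benefit only, no harm boundary | 0.0523 | 0.0477 |
| 0.01 for benefit, 0.001 for harm | 0.0524 | 0.0476 |
| 0.01, both directions | 0.0545 | 0.0453 |

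The benefit-only rows are closest to section 18, which speaks of differences showing efficacy. The symmetric row is the upper case.

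Moving the information fraction from 0.45 to 0.56 changes the symmetric 0.01 result from 0.0551 to 0.0539 and the benefit-only result (no harm boundary) from 0.0526 to 0.0519. Binomial simulation with 63 per arm at the interim and 125 at the end, at true rates of 28%, 37%, 46% and 60%, gives 0.0544, 0.0550, 0.0534 and 0.0527 for the symmetric 0.01 rule. A single final test alone gives 0.0498, 0.0507, 0.0491 and 0.0484.

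**3. Chance of crossing at the interim under 46% versus 28%.**

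P(cross) = Φ[(0.18 − c·SE0)/SE1], with SE0 = √(2·0.37·0.63/n) and SE1 = √((0.46·0.54 + 0.28·0.72)/n)

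- All 126 evaluable, n = 63: SE0 = 0.0860, SE1 = 0.0845.
  - At 0.001: c·SE0 = 0.283, (0.18 − 0.283)/0.0845 = −1.22, chance 11%.
  - At 0.01: c·SE0 = 0.222, (0.18 − 0.222)/0.0845 = −0.49, chance 31%.
- 10% not evaluable (the allowance for early death in protocol 14.2), 126 × 0.9 = 113.4, so n of 56 to 57. With n = 56: SE0 = 0.0912, SE1 = 0.0896.
  - At 0.001: (0.18 − 0.300)/0.0896 = −1.34, chance 9%.
  - At 0.01: (0.18 − 0.235)/0.0896 = −0.61, chance 27%.

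The chance of landing between the two thresholds is therefore 31 − 11 = 20%, or 27 − 9 = 18%. With 63 per arm that band is an observed difference of roughly 22 to 28 percentage points.

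**The case against.** The strongest reply is that there is really one rule. Section 18 is a quality-assurance narrative; its figure is an example, it names no boundary method and it sets no error rate. Eight other places, including the DSMB's own section (13.5), the statistics section and the later SAP, give 0.001. A board working from those would have little doubt, and in any case it only advises.

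Most of this stands. A reader might infer that two thresholds are equally in force; the wording does not support that. What survives is that an illustration ten times looser than the rule misdescribes it, in current text, with no precedence clause.

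Three other stronger readings also fail.

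- A reader might conclude that the trial's 5% error rate is broken. The excess arises only if the board acts on section 18, and it is not the 6% that adding 0.01 and 0.05 would suggest, because the two statistics are correlated. Nor is 5.45% the only candidate: section 18 concerns efficacy, and the benefit-only calculation about halves the excess. The 0.001 rule is itself slightly above 5%.
- A reader might take 31% as a false-positive risk. It is a crossing probability when the planned effect is real.
- A reader might say that the looser threshold gives a more exaggerated estimate in each stopped trial. The reverse holds: a stop at 0.001 needs an observed difference of about 28 points, a stop at 0.01 about 22. The looser rule makes such early stops about three times as common.

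**Conclusion.** Wrong as written, and a should-fix: an internal inconsistency in a decision threshold, not an arithmetic error. If 0.01 were used with the final test at 0.05, type I error would be about 5.2% to 5.45% instead of 5.02%, an excess over 5% of roughly 0.2 to 0.45 percentage points. The larger effect is on early stopping under the planned effect: about 27–31% instead of 9–11%.

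These figures assume one look, the primary outcome only, information proportional to infants randomised, and no binding futility rule. The lower crossing figures assume 10% are not evaluable. The SAP's while-alive handling of early deaths (1.4.1) would keep such infants in the analysis, which points to the upper figures.

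The documents do not say whether the look took place or which threshold was used. Version 2.1 notes that close-out had begun at some sites, and the SAP is dated 27/04/22, so a reader might infer that the board had already acted on one figure or the other. Nothing in the text supports either inference.

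**What to change.** In protocol section 18, replace P<0.01 with P<0.001, cross-refer to 14.8, and name death before hospital discharge as the other monitored outcome. This brings section 18 into line with the rule already named in 14.7 and 14.8 and changes neither the sample size nor the final level.

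If the interim look has already taken place, also record which threshold the DSMB applied, either in SAP section 6 or as an explanatory statement in the final report under protocol 14.10. At that stage the section 18 edit serves mainly to set the record straight.

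The cost is one corrected line and, where needed, one sentence of record. The supplied documents mention no DSMB charter, so none is called for here.

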## **19 AUDITS AND INSPECTIONS**

This trial may be subject to internal or external auditing or inspections procedure to ensure adherence to GCP. Access to all trial-related documents will be given at that time.

A quality assurance audit may be conducted by the sponsor or its agent at any time during, or shortly after, the study. The investigator will permit an independent audit by an auditor mandated by Sponsor, after reasonable notice. The purpose of an audit is to confirm that the study is conducted as per protocol, GCP and applicable regulatory requirements, that the rights and well-being of the patients enrolled have been protected, and that the data relevant for the evaluation of the investigational medicinal product have been captured, processed and reported in compliance with the planned arrangements. The investigator will permit direct access to all study documents, drug accountability records, medical records and source data.

Regulatory authorities may perform an inspection of the study up to several years after its completion. If an inspection is announced the Sponsor will be informed immediately.

## **20 ETHICS**

Ethical approval will be sought by each participating centre. Approval will be obtained prior to commencement of the trial and in compliance with Ethics committee's requirements.

### **20.1 Declaration of Helsinki**

The sponsor will ensure that this study is conducted in accordance with the ethical principles that have their origins in the Declaration of Helsinki.

### **20.2 Good Clinical Practice**

This study will be conducted in accordance with Good Clinical Practice (GCP), as defined by the International Conference on Harmonisation (ICH) and in accordance with the ethical principles underlying European Union Directive 2001/20/EC and 2005/28/EC.

### **20.3 Approvals**

Required documents including the protocol, informed consent form, subject information leaflet, investigational medicinal product dossier, investigators brochure and any other required documents will be submitted to a recognised research ethics committee and the competent authority for written approval.

The sponsor will submit and obtain approval from the above parties for substantial amendments to the original approved documents.

### **20.4 Informed consent**

Prior to delivery a member of the research team or other senior doctor will approach parent(s)/guardian(s) of eligible infants to inform them about the study. The team member will explain the purpose and nature of the study and provide written information for the parent(s)/guardian(s) to keep. Parent(s)/guardian(s) will be offered the opportunity to have another family member or support person present while the study is explained. If English is not their first language, they will also be offered the opportunity to have an interpreter present while the study is explained.

Written consent for enrolment of the infant in the study will then be sought, where applicable, by both parents/guardians prior to any study-related activities, or as per local requirements and as approved by the ethics committee for the site. Parents will be informed that they may withdraw their child from the study at any time should they so wish; and that a decision not to consent to their infants participation in the study or to withdraw their infant from the study once enrolled will not affect their infants access to the best available treatment and care at the birth hospital or other hospital to which they might be referred. Consent forms will be kept securely and a copy will be provided to the parents for their records.

## **20.5 Benefits and risks assessment**

We will perform this study to establish whether giving preterm infants surfactant into their oropharynx at birth reduces their need for subsequent intubation in the first 5 days of life.

Potential benefits of the intervention include:

- Easier method of surfactant administration
- Cheaper method of surfactant administration
- Less discomfort to infants during surfactant administration
- May reduce costs associated with ventilation
- May reduce adverse effects of ventilation

All babies in both groups will be closely watched to see if they need extra treatment for their RDS at any stage, including surfactant given endotracheally. The babies will be treated equally and given whatever treatment is necessary, whether or not they have already been given surfactant into the oropharynx.

Preterm babies who are intubated and receive mechanical ventilation are at risk of chronic lung disease of prematurity. Avoidance of mechanical ventilation and administration of surfactant through less invasive techniques has been an important area of research over the last number of years.

There is evidence from animal (22, 23) and human studies (4, 5) that suggest that pharyngeal administration of surfactant to newborn infants at risk of RDS is safe and may be effective. A recent Cochrane Review (24) highlighted the need for a well-designed randomised control trial to address this question.

An independent DSMB will be established to perform ongoing safety surveillance and to perform interim analyses on the study data. The DSMB will meet on a regular basis and will review the frequency and severity of adverse events in both treatment groups. If they observe any significant excess of serious adverse events in the intervention group associated with the intervention, they may recommend to prematurely terminate the trial on the basis of serious safety concerns. Interim analysis of the primary endpoint and the secondary endpoint death before hospital discharge will be performed by the DSMB. This will be performed once half the planned sample (126 participants) have completed the trial.

